## Abstract

**Background:**

A decision of the Federal Joint Committee Germany in 2008 stated that negative pressure wound therapy is not accepted as a standard therapy for full reimbursement by the health insurance companies in Germany. This decision is based on the final report of the Institute for Quality and Efficiency in Health Care in 2006, which demonstrated through systematic reviews and meta-analysis of previous study projects, that an insufficient state of evidence regarding the use of negative pressure wound therapy for the treatment of acute and chronic wounds exists. Further studies were therefore indicated.

**Methods/design:**

The study is designed as a multinational, multicenter, prospective randomized controlled, adaptive design, clinical superiority trial, with blinded photographic analysis of the primary endpoint. Efficacy and effectiveness of negative pressure wound therapy for wounds in both medical sectors (in- and outpatient care) will be evaluated. The trial compares the treatment outcome of the application of a technical medical device which is based on the principle of negative pressure wound therapy (intervention group) and standard conventional wound therapy (control group) in the treatment of subcutaneous abdominal wounds after surgery. The aim of the SAWHI-VAC® study is to compare the clinical, safety and economic results of both treatment arms.

**Discussion:**

The study project is designed and conducted with the aim of providing solid evidence regarding the efficacy of negative pressure wound therapy. Study results will be provided until the end of 2014 to contribute to the final decision of the Federal Joint Committee Germany regarding the general admission of negative pressure wound therapy as a standard of performance within both medical sectors.

**Trial registration:**

Clinical Trials.gov NCT01528033

German Clinical Trials Register DRKS00000648

## Background

### The medical problem

Wound healing impairment after surgical procedures is a common problem in health care. Complications associated with surgical incisions range from the annoying to the life threatening, and can be more common and serious than those related to the primary surgical procedure. These complications include wound healing disorders caused by factors due to the surgical procedure itself, by patient-related factors, or both. These factors are typically interrelated, complex in nature, and often difficult to prevent or to treat successfully. The most common post-operative wound healing impairments are seroma or hematoma, necrosis of wound margins or adjacent soft tissue, infections, all with potential to cause dehiscence of the primarily closed wound. The occurrence of wound healing impairment of the abdominal wall represents a multidisciplinary, treatment- and cost-intensive problem in clinical life whether it is caused by infectious or non-infectious factors [1-3]. Only a few clinical trials have been conducted regarding the use of negative pressure wound therapy (NPWT) for subcutaneous abdominal wound healing impairment [4-7] or for example, the adjunctive management of abdominal wounds with exposed and known infected synthetic mesh [8]; thus, a randomized controlled clinical trial (RCT) of high quality that is able to make a statement concerning efficacy and effectiveness of this innovative therapy option is still lacking.

### Vacuum-assisted wound closure (V.A.C.®)

Basic science studies demonstrated positive effects of NPWT on wound healing [9,10] and many case reports and case series document broad use of V.A.C.® (http://www.kci-medical.co.uk/uk-eng/home) in various clinical settings [11].

Regarding the clinical results and mechanisms of action of NPWT, the literature provides evidence with regards to V.A.C.® Therapy’s effectiveness in chronic wounds such as in diabetic foot wounds, pressure ulcers and lower extremity ulcers [12]. Additionally, V.A.C.® Therapy is used in the treatment of a variety of acute wounds, including abdominal wounds [13], surgical and dehisced wounds [13-15], grafts and flaps [16,17], deep sternal wounds [18-20] and partial thickness burns [21,22].

### Recent history

When compared to standard conventional wound therapy (SCWT), most of the published literature confirms the advantage of negative pressure wound therapy (NPWT), also called vacuum assisted wound closure, but sufficient proof of efficacy and effectiveness is lacking [12,23]. The Federal Joint Committee (G-BA) is the highest decision-making body of the joint self-government of physicians, dentists, hospitals and health insurance funds in Germany. The G-BA faced this situation by commissioning a report on efficacy and effectiveness of NPWT by the Institute for Quality and Efficiency in Health Care (IQWiG). The final IQWiG-reports [24,25] concluded that, in spite of some indications that NPWT may improve wound healing, the methodological quality of the so far performed trials is unsatisfactory and thus the body of evidence available is insufficient, more specifically in the post-acute care setting. In 2011, Peinemann and Sauerland updated the systematic literature review [26] and concluded that although there may be a positive effect, clear evidence for efficacy and effectiveness of NPWT is still missing and RCTs of high quality are still needed to evaluate the benefit of this wound treatment option. Since the updated review, only a few RCTs on NPWT with the objective to achieve complete wound closure have been performed [27,28]. Thus, there is still a need for a RCT of high quality to contribute to the decision about the benefit of the use of NPWT for wound healing.

### Study objectives and purpose

This RCT was designed to evaluate the efficacy and effectiveness of V.A.C.® Therapy for the treatment of subcutaneous abdominal wound healing impairment after surgery. Furthermore it will collect data that will provide a basis for subsequent efficiency analyses. Moreover, this trial seeks to evaluate the use of V.A.C.® Therapy in the acute to post-acute environment, particularly because wound healing occurs across the continuum of care and often continues after a patient is released from the hospital to homecare or other community-based care. Thus, there is a need to identify the outcomes and benefits of V.A.C.® Therapy when compared to SCWT when used across these care settings.

This trial is designed to comply with all quality requirements of IQWiG and G-BA as well as other European authorities.

Study results aspire to contribute to the benefit assessment of the IQWiG and the final decision of the G-BA regarding the eligibility of V.A.C.® Therapy to be a standard treatment recognized by German health insurance companies for full reimbursement in both medical sectors.

## Methods/design

The SAWHI-V.A.C.®-study is designed as a multinational, multicenter, randomized controlled, clinical superiority trial, with blinded photographic analysis of the primary endpoint. The trial will be performed in Germany, the Netherlands, Belgium, United Kingdom and Austria.

### Phase and classification of the trial

The study is classified as an examination of the clinical application of a CE-marked medical device with risk category IIb.

According to the German Medical Device Act (MPG) the trial is classified as an exemption to clinical investigation according to section (§) 23b MPG. This is due to the fact, that the investigational device is CE-marked, will only be operated within intended use and there will be no additional invasive or otherwise straining examinations. Examination results will only be documented if collected within clinical routine.

Ethical approval of the main ethical committee (EC): Ethical Committee of the University of Witten-Herdecke, has been fully granted without any conditions. Due to performing the trial according to section (§) 23b MPG, further participating centers in Germany will only receive a consultation for the respective main clinical investigator according to professional law. Ethical approval of participating centers in Germany is not applicable. Furthermore, until the actual time point, full EC approval was granted by the EC of the Academisch Ziekenhuis Maastricht (Netherlands) and by the NRES Committee East Midlands - Leicester, England (NHS). From each trial participant, a written informed consent will be obtained under the conditions set forth in ICH-GCP guidelines.

### Randomization

Randomization to treatment arms will be performed at a 1:1 ratio. Randomization will be performed via a centralized system with an Internet-based tool. Patients will be randomized dynamically. The permuted block sizes will randomly vary between 2, 4, and 6.

### Stratification

Stratification will take place by study center and then also subsequently by wound size (cm^3^) within study center. Wound size categories or strata to be considered will be wounds ≤ 60 cm^3^ and wounds > 60 cm^3^.

### Primary endpoint

The primary endpoint of this trial is defined as time (number of days) to achieve complete wound closure in study participants where closure was observed on or before day 42 and was confirmed to have been sustained for a minimum of 14 subsequent days. Complete wound closure is defined as 100% epithelialization, no drainage from the wound, no need for adjuvant therapy or dressing and no presence of sutures. Complete wound closure has to be confirmed after a minimum of 14 consecutive days. The clinically determined primary endpoint will be verified through blinded assessment of wound photos by observers that are independent from the clinical trial.

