### Secondary clinical endpoints

The incidence of wound closure achieved within each treatment arm will be evaluated after a maximum study observation/treatment period of 42 days. These wound closures have to be confirmed as being sustained for a minimum of 14 subsequent days. This will be conducted via blinded photographic analysis. Recurrence of wound opening after initial closure and confirmed wound closure will be assessed and compared between the treatment groups. Reduction of wound size over time will be evaluated using reduction in wound volume and wound surface area over time.

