### Blinding

Due to the physical differences between the treatment regimens, it is not possible to blind either participant or physician to the treatment. To address issues of blinding, wound photo documentation will be obtained during the trial and confirmation of wound closure will be assessed via blinded assessment of photos by independent observers, which will serve as the method of primary endpoint analysis.

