### SAWHI-website, photo documentation platform and verification of clinical wound size estimation

A study-website has been set up that contains all relevant information about the trial as well as a personal login area for each participating study center and a web-based photo documentation platform for wound photographs of study participants. The website can be found using the uniform resource locator http://www.sawhi.com. Wound photographs will be uploaded by study sites for each trial visit. The Wound Healing Analyzing Tool (WHAT) has been integrated within the platform. A centralized wound analysis of anonymized photographs (blinded assessment of wound photos) will be performed, which facilitates the objective evaluation of wound healing processes. Secondary endpoints (numerical parameters) like circumference (mm), area (mm^2^), maximum length (mm), and height (mm) will be calculated from the wound image using WHAT whereas the application of the system also will be performed by blinded independent assessors.

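### The primary endpoint is described as clinician-determined and photo-verified in one section and as analysed by blinded photo reading in others; read together, the closure date in the log-rank test is still set by an unblinded clinician

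*Protocol article*

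**What the plan says.** All references are to the protocol article.

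- **Primary endpoint.** The endpoint is "time (number of days) to achieve complete wound closure in study participants where closure was observed on or before day 42", with closure sustained for at least 14 further days. Closure requires "100% epithelialization, no drainage from the wound, no need for adjuvant therapy or dressing and no presence of sutures". On who decides: "The clinically determined primary endpoint will be verified through blinded assessment of wound photos by observers that are independent from the clinical trial".
- **Blinding.** Because of the physical differences between treatments, "it is not possible to blind either participant or physician to the treatment". The remedy offered is that confirmation of closure rests on "blinded assessment of photos by independent observers, which will serve as the method of primary endpoint analysis".
- **Abstract (Methods/design) and the opening of Methods/design.** Both describe the primary endpoint as analysed photographically by blinded readers.
- **Secondary clinical endpoints.** On the incidence of confirmed closure by Day 42: "This will be conducted via blinded photographic analysis".
- **SAWHI-website section.** "Wound photographs will be uploaded by study sites for each trial visit". A centralised blinded analysis of anonymised photographs is planned, and blinded independent assessors apply the wound-measurement tool.
- **Type of analysis.** The primary comparison is a log-rank test of time to closure.

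**The concern.** The section that defines the endpoint gives the determination to the treating side and a checking role to the photo readers. The Blinding section and the two design statements present the photo reading as the analysis itself. It matters which description governs, because the endpoint is a number of days and the date enters the log-rank test directly.

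A check on a declared closure can reject a false one. As worded, it does not give the readers the date. If clinicians who know the arm call control wounds closed a little later, or less often, the difference would look like a device benefit. Several closure components, such as the need for a dressing, are bedside judgements on which knowledge of the arm could act. The trial is meant to supply high-quality evidence to the German assessment bodies, and blinded assessment is its stated answer to the lack of treatment blinding.

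**Working it through.** **1. The passages side by side**

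| Section | Source of the closure call | Role of the blinded photo reading |
|---|---|---|
| Primary endpoint | Clinician | Verifies |
| Blinding | Not stated | Confirms closure, and is the method of primary endpoint analysis |
| Abstract; Methods/design opening | Not stated | Analysis of the primary endpoint |
| Secondary clinical endpoints | Not stated | Conducts the assessment of closure incidence |

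*Reading A, two steps:* the clinician declares closure and the photos confirm it. All the sections fit this, but the date is then the clinician's.

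*Reading B, photos as the source:* the readers fix the event and its date. The Blinding section and the design statements fit this; the term used for the endpoint in the Primary endpoint section does not fit easily.

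Only Reading B takes the date away from the unblinded clinician.

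**2. The plan's own figure, which supplies the setting**

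Inputs from Determination of sample size: closure 50% against 62.5% at Day 42, 80% power, α = 0.05 or 0.048 (taken as two-sided).

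n = [z(1−α/2)·√(2·p̄·(1−p̄)) + z(0.80)·√(p1(1−p1) + p2(1−p2))]² / (p2−p1)²

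with p̄ = (0.50 + 0.625)/2 = 0.5625.

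- α = 0.05: (1.960·0.7016 + 0.8416·0.6960)² / 0.125² = 246.1; the plan states 246.
- α = 0.048: (1.977·0.7016 + 0.8416·0.6960)² / 0.125² = 249.1; the plan states 249.

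The sample size reproduces and is not in dispute.

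**3. Illustration with no true effect**

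From the plan: 249 per arm, 42-day horizon, log-rank test at 0.048. Assumed: two-sided testing, 56.25% closure in both arms (the mean of the plan's two rates), exponential closure times rounded up to whole days, and every distortion below, each applied to the control arm only. Ranges cover independent runs of 8,000 to 40,000 simulated trials.

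| Assumed distortion in control arm | Two-sided error |
|---|---|
| None | 4.6-5.0% |
| Dated 2 days late, no closure lost (dates capped at Day 42) | about 6% |
| Dated 3 days late, no closure lost | about 7.5% |
| Dated 2 days late, late ones fall past Day 42 | about 9% |
| Dated 3 days late, late ones fall past Day 42 | 13.5-14.4% |
| 5% of closures never declared or read | 8.7-9.3% |
| 10% of closures never declared or read | 22.2-23.3% |

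Nearly all the excess in the lower four rows favours the device.

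**4. Why the lower rows are larger**

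They remove events as well as moving dates. With an exponential closure time, the share closed by day d is 1 − 0.4375^(d/42).

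- 2 days late: 1 − 0.4375^(40/42) = 54.5%, a loss of about 1.8 points from 56.25%.
- 3 days late: 1 − 0.4375^(39/42) = 53.6%, a loss of about 2.7 points.
- 5% undeclared: 0.95 × 56.25% = 53.4%, a loss of about 2.8 points.
- 10% undeclared: 0.90 × 56.25% = 50.6%, a loss of about 5.6 points.

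**5. The mirror case**

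Here device-arm closures are dated early, with 50% closing in each arm. If only the dates of true closures move, error in the device's favour (nominal 2.4%) is about 4-5% for 2 days and 5-6% for 3 days. The direction is the same and the size similarly modest.

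**The case against.** The strongest reply is that the sections do not conflict. The Blinding section speaks of confirming closure and the Primary endpoint section of verifying it; both fit a site call followed by a blinded check. This stands: a reader might infer two different, flatly opposed endpoints, and the text does not support that. It does not settle the date, which on this reading remains the clinician's.

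Second, a reader might infer that the photo readers may only strike out declared closures and can never add or re-date one. The article does not say so. It does not limit which photos are read, photos exist for every visit, and closure incidence is said to be assessed photographically. The undeclared-closure rows therefore apply only if declared closures alone are read.

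Third, a reader might take 9-14% as the effect of biased dates alone. It is not: most of that inflation comes from closures lost past Day 42. Dates alone give about 6-7%.

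Fourth, an adjudication rule may well stand in the full protocol, the analysis plan or a reader charter. That is fair, and its absence from an article is not the point. The point is that the article's own statements differ on which source determines the primary endpoint, and that determine-then-verify leaves part of the bias which the Blinding section offers the photos to address.

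Finally, photos cannot settle drainage or the need for a dressing or adjuvant therapy, so no photo-based rule blinds the whole endpoint. This also stands and limits what the fix can claim.

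**Conclusion.** The point holds as a need to reconcile the wording and as a residual risk of bias. The sections are compatible if read as two steps, but on that reading an unblinded clinician sets the date used in the primary test.

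The documents give no size for the bias. Under the assumed control-arm delays of 2 to 3 days, error rises from about 5% to about 6-7% through dates alone. The figures of about 9-14% need closures to be pushed past Day 42 as well, and about 9-23% needs 5-10% of control closures to be neither declared nor read. These figures show sensitivity to assumed behaviour; they do not show that the trial has such an error rate. The sample size is unaffected. A change is worth making because blinded assessment is the plan's main protection for an open-label comparison.

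**What to change.** Reconcile the Primary endpoint section with the Blinding section, and carry the same wording into the full protocol and analysis plan:

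- Blinded readers assess the photos of every visit in both arms, without seeing the clinician's call.
- The primary event date is the first visit that the readers judge fully epithelialised with no visible sutures, and at which the site has recorded no drainage and no need for a dressing or adjuvant therapy.
- The 14-day confirmation is judged by the same blinded reading, applied to the confirmation-visit photos.
- The blinded reading governs any disagreement on the components a photo can show.
- Time to closure as determined by the clinician is reported as a sensitivity analysis.
- The text states openly that drainage and the need for a dressing or adjuvant therapy remain unblinded site judgements, so the bias is reduced rather than eliminated.

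The cost is event dates resolved only to the visit, and more reading for assessors who are already in place. Photos are already uploaded for each visit. The article does not give the visit spacing, so the loss of date precision cannot be quantified from it.

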### Secondary clinical endpoints

The incidence of wound closure achieved within each treatment arm will be evaluated after a maximum study observation/treatment period of 42 days. These wound closures have to be confirmed as being sustained for a minimum of 14 subsequent days. This will be conducted via blinded photographic analysis. Recurrence of wound opening after initial closure and confirmed wound closure will be assessed and compared between the treatment groups. Reduction of wound size over time will be evaluated using reduction in wound volume and wound surface area over time.

### Safety endpoints

Incidence of serious adverse events (SAEs) including mortality of any cause within 132 days from the time of initiation of therapy, incidence of device-related events (ADEs), wound-related adverse events (AEs) and incidence of unsustained closure within the study treatment time of 42 days are considered to be safety endpoints of this trial.

### Patient reported outcome

Instruments and assessments used for measurement of Patient Reported Outcome (PRO) of the SAWHI-study focus on the constructs ‘Quality of life’ (QoL) and ‘Reports and Ratings of health care’ (Patient Satisfaction). QoL is measured by using a multidimensional questionnaire assessing a combination of aspects of impairments and disability and reflects a patient’s health status. QoL will be measured using the SF-36v2 questionnaire at Day 42 (end of maximum treatment/observation time) or at wound closure visit, hospital discharge, and at the general follow-up visit. Patient Satisfaction covers a structured participant self-report and a valuation of the disease-specific healthcare [29]. Furthermore, this point includes participants’ valuation of the treatment result with regard to scarring and the cosmetic result. The participant will be asked about the general estimation of therapy progression and detailed treatment satisfaction. This item will be evaluated by using a self-constructed questionnaire on the basis of specific scales of the Cologne Patient Questionnaire [30]. The Cologne Patient Questionnaire has formerly been used to develop a theory-based and empirically tested instrument for measuring patient-reported ‘psychosocial care by physicians’ [31] and represents an ideal basis for development of a specific questionnaire for participant satisfaction of this trial. Patient Satisfaction will be evaluated during general follow-up visits. Furthermore, during study visits, participants will be asked to provide their assessments of pain with a numerical rating scale. Participants will be asked to provide an estimate of their wound-associated pain of the last 24 hours.

### Health economic endpoints

Additionally to the evaluation of clinical treatment effectiveness, a prospective assessment of health economic issues will be performed. This evaluation includes the assessment of parameters relevant for inpatient and outpatient resource use (resource utilization). A detailed baseline data acquisition regarding underlying disease and intervention will create the basis for further assessments of health development and resource use. Participants’ co-morbidities will be documented using a separate, standardized case report form (CRF) sheet. The category direct medical resource use (direct medical costs) includes the resource use that results directly from wound treatment or wound-specific therapy. General and specific clinical diagnostics, relevant medication (in particular analgesics and antibiotics), specific wound therapy, number and type of debridement, residential treatment and medical attendance, outpatient treatment and medical attendance will be analyzed. Surgical reinterventions and rehospitalizations are especially a burden for health care and will be evaluated during the study. Resource use (cost) that is not directly associated with disease treatment is considered as indirect resource use (cost). This includes the evaluation of restrictions of productivity besides absence from the workplace (activities of daily living) and nonproductive time for those who are gainfully employed.

